
## Discussion

Our controlled cross-sectional epidemiological study aims to compare the prevalence of PPD in fathers within the first year after childbirth with the prevalence of depressive symptoms in a matched sample of men without new paternity. Furthermore, our study should reveal differences regarding the prevalence of PPD in fathers in different time periods within one year after childbirth. Additionally, potential male-specific symptoms and risk factors of PPD in fathers will be investigated. A further goal is to assess the current healthcare situation of fathers with PPD in Germany. Our findings will contribute to closing the above-mentioned research gaps and offer possibilities to refine healthcare options for fathers with PPD. Compared to previous studies, our study has several methodological strengths. A central advantage is the direct comparison of the prevalence of PPD in fathers of an infant with the prevalence of depressive symptoms in a matched group of men without recent paternity from the general population. The simultaneous detection of depressive symptoms using the same measurement instrument will minimize the risk of producing an estimation bias of the relative prevalence of PPD and thus increase the external validity of the results. The large sample size compared to previous studies will allow us to perform a variety of subgroup analyses. Furthermore, the large sample size and the recording of the date of childbirth and the date of responding to our questionnaire will allow us to examine prevalence differences for several time periods within one year after childbirth and to analyze specific symptoms of PPD and risk factors. A further advantage of our study lies in the consideration of the healthcare situation of fathers with PPD in Germany – an issue that has not been considered in the research so far. By examining these aspects, low-threshold service access can be revealed, enabling important hints to be derived for the development of adequate care options for fathers with PPD. The identification of risk factors for the development of PPD in fathers will allow an early and specific treatment for these men through the utilization of adequate healthcare offers. Finally, genetic and epigenetic risk patterns of PPD to be identified in the exploratory add-on study might serve as future biomarkers for early interventions or even personalized preventive measures in men at risk of PPD.

A potential limitation lies in the method of recruitment, which could produce a selection bias in the sample and thus restrict the external validity of the results. A further limitation is that study participants have to self-administer a high number of measurement instruments. This might hinder the feasibility of the trial and reduce the response rate. We have tried to address this issue by naming a contact person from the study team in case of questions, by giving examples on how to answer the questionnaire, and by reducing the questionnaire to relevant aspects. As we will also assess the general health status and other diagnoses such as anxiety, it will be possible to detect some of the potential confounding factors.

Our study will provide insights into the issue of PPD in fathers. Currently, there is no study on PPD using a matched control group. Studies conducted to date compared their results with historical control data, which carries the risk of over- or underestimation of the relative frequency of depressive symptoms after childbirth. A simultaneous detection of depressive symptoms, of symptomatology, and of risk factors using the same instruments will enhance the comparability of the results and thus ensure the scientific quality of the concluding statements. Surveying the healthcare situation will provide opportunities for the practice-oriented design of current care and thus information on the development of screening methods and healthcare concepts. Based on the findings of our study, further studies should address the standardization of measurement methods to identify PPD as well as male-specific healthcare interventions in fathers.

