## Methods/design

### Study design

A controlled, cross-sectional epidemiological survey in men with new paternity within one year prior to this survey (group 1: fathers of an infant) and a matched sample of men without a newborn child within one year prior to this survey (group 2: control group) will be conducted via postal questionnaires. The aim is to compare the prevalence of PPD in fathers within the first year after childbirth to the prevalence of depressive symptoms in a matched sample of men without a newborn child. As study regions, we chose two cities in Southwestern Germany with varying populations regarding birthrate, employment status, socioeconomic structure, and nationality of inhabitants: Freiburg and Mannheim, with 228,000 and 320,000 inhabitants, respectively. As social factors may influence the development of PPD in fathers and of depressive symptoms in men without new paternity, the use of two structurally different cities as study regions allows the generalizability of the results to be investigated.

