#### Risk factors

To identify risk factors of PPD, various secondary objectives will be evaluated. The course of disease was chosen as a secondary objective, as numerous studies have demonstrated its moderating influence on the development of depressive symptoms. The course of disease is not recorded in the PHQ-9 and will therefore be assessed using additional items regarding the duration of the current episode and previous episodes.

To detect present anxiety symptoms, the Adult Separation Anxiety Questionnaire (ASA-27, [50]) and the Anxiety Sensitivity Index (ASI, [51]) will be administered. The ASA-27 assesses symptoms of separation anxiety in adulthood. Principal components analysis of the ASA-27 revealed a coherent construct of separation anxiety with high internal consistency (Cronbach’s alpha = .95) and high retest reliability (r = .86; *P* < .001) [50]. The ASI questionnaire measures individuals’ tendency to interpret anxiety-associated physical sensations as threatening. It has an internal consistency of .88 (Cronbach’s alpha) and .85 (Guttman split-half reliability). Furthermore, the ASI is factorially independent of other anxiety measures [52].

Global assessments of the subjective judgment of the child’s and of the mother’s health status as possible influencing variables will be recorded using self-constructed items. Additionally, it will be asked whether a diagnosis of maternal postpartum depression is present.

The normative gender role orientation of the study participants will be evaluated using the Questionnaire of Normative Gender Role Attitudes (NGRO [44];). The NGRO focuses on internalized, personal gender role models and locates respondents between the poles of traditional vs. egalitarian standard expression. The internal consistency of the 29 items version of the NGRO is high (Cronbach’s alpha = .91). The calculation of the retest reliability gave a coefficient of r = .76 [44].

Social support will be measured using the standardized German short form of the Social Support Questionnaire (F-SozU-K-14 [45];), a unidimensional scale assessing support as perceived or anticipated support, with a focus on emotional and practical support and social integration. Additionally, the use of support systems (e.g. support from grandparents, infant care facilities, etc.) will be examined using self-constructed items.

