#### Analyses

Relative frequencies will be calculated for nominal-scaled variables. For ordinal-scaled and non-normally distributed interval-scaled measurements, the median is used as the preferred measure of central tendency. For interval-scaled variables, the arithmetic mean and standard deviations will be calculated. The choice of the respective statistical method for group comparisons depends on the scale level of the dependent variable. Although a matched sampling will be performed, this information cannot be used in the evaluation due to the anonymity of the survey. The evaluation therefore requires the use of independent samples techniques. Nominal distributions will be compared using Chi-square and Fisher’s exact tests. Parametric tests (t-test, analysis of variance) will be used for interval-scaled measurements. The effect of socio-demographic and other influencing factors will be calculated using logistic regressions.

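### A one-time survey shows correlates of current symptoms, not risk factors for developing PPD, for every factor self-rated alongside the PHQ-9

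*Protocol article*

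**What the plan says.** Under Study design the study is "A controlled, cross-sectional epidemiological survey in men with new paternity within one year prior to this survey", set against a matched sample of men without a newborn. Recruitment describes one mailing with one questionnaire. The article mentions no earlier or later wave.

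The Risk factors section and Table 1 list what will be examined. Several entries are current states or perceptions. One begins "To detect present anxiety symptoms, the Adult Separation Anxiety Questionnaire". Others are anxiety sensitivity, self-efficacy, social support as the respondent perceives it, sleep quality, and ratings of his own, the child's and the mother's health. The same section includes the course of disease because "numerous studies have demonstrated its moderating influence on the development of depressive symptoms", and says that it "will therefore be assessed using additional items regarding the duration of the current episode and previous episodes".

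The Analyses section states: "The effect of socio-demographic and other influencing factors will be calculated using logistic regressions". The Discussion then draws the conclusion about development and treatment ("The identification of risk factors for the development of PPD in fathers will allow an early and specific treatment for these men") and adds as a merit: "A simultaneous detection of depressive symptoms, of symptomatology, and of risk factors using the same instruments will enhance the comparability of the results".

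**The concern.** A risk factor for developing a condition has to precede it. When a man rates his self-efficacy, support, anxiety, sleep and family's health in the same questionnaire as his depressive symptoms, low mood may colour each answer. An association between such a scale and the PHQ-9 fits three accounts: the factor contributes to depression, depression changes the factor, or both share a cause. A single wave cannot separate them.

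At stake is a stated secondary objective and the use the Discussion makes of it. The scales most sensitive to mood could come out as the leading risk factors, and the Discussion would direct early treatment by them. Duration of the current episode is a special case. It is a feature of the outcome, defined only for men who already have an episode, yet it is listed under Risk factors.

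**Working it through.** **Timing of the candidate factors.** The rows of Table 1 can be sorted by when the thing measured was settled.

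- *Before the current symptoms, at least plausibly:* previous depressive episodes, socio-demographic data, planned or unplanned pregnancy, artificial insemination, complications, prematurity, multiple birth, mode of delivery. All are reported afterwards, so recall matters, and depression that began before the birth would weaken the order for the birth items.
- *At the same time as the PHQ-9:* GSE, F-SozU-K-14, ASA-27, ASI, general sleep quality, own health, child's and mother's health as rated by the father.
- *Unclear or mixed:* gender-role attitudes (NGRO), the involvement row, and the maternal diagnosis.
- *Part of the outcome:* presence and duration of the current episode.

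The claim about development could be defended for the first list. It cannot be for the second.

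**The Discussion set against the design.** Simultaneous measurement with the same instruments does make prevalence comparable between fathers and controls, so the statement is sound for the primary objective. The Discussion extends it to risk factors, where simultaneity is what removes the time order. Its limitations cover selection bias, questionnaire burden and, in effect, confounding. Temporal order and reverse causation are absent. Anxiety also has two roles in the article, as a potential risk factor under Study design and as a potential confounder in the Discussion. The possibility that it is a consequence is not raised.

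**How easily a consequence would appear as a risk factor.** This is an illustration; the plan gives no figure for this objective.

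Inputs from Sample size calculation: 9200 men contacted, 4600 of them fathers; about 75% non-response; prevalence in fathers 8.0%; significance level 0.05, taken here as two-sided.

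- All respondents: 9200 × (1 − 0.75) = 2300, which agrees with the plan's required total.
- Fathers responding: 4600 × 0.25 = 1150.
- Cases: 1150 × 0.08 = 92. Non-cases: 1150 − 92 = 1058.

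Assume a scale that plays no causal part, and that being depressed shifts its mean by d standard deviations.

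- Standard error of the standardised difference: √(1/92 + 1/1058) = √0.011815 = 0.1087.
- Probability of a significant association: Φ(d / 0.1087 − 1.96).
- Odds ratio per SD, for normal scores with equal variance: exp(d).

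| d | d / 0.1087 | Probability significant | Odds ratio per SD |
|---|---|---|---|
| 0.1 | 0.92 | 15% | 1.11 |
| 0.2 | 1.84 | 45% | 1.22 |
| 0.3 | 2.76 | 79% | 1.35 |
| 0.5 | 4.60 | over 99% | 1.65 |

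The documents do not give d, so the range is shown. A modest shift caused by depression is enough to produce a significant odds ratio that says nothing about development.

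**The case against.** The strongest reply has four parts.

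- **The article is open about its design and often cautious.** It calls the study cross-sectional throughout, the factors potential under Study design, and the health ratings possible influences under Risk factors. Effect is ordinary regression vocabulary, and the treatment sentence is outlook. This stands as mitigation, but the Discussion drops the caution and claims a merit that the design does not have for this objective.
- **Some scales are closer to traits than states.** The article gives retest coefficients of .86 for the ASA-27 and .76 for the NGRO and describes the ASI as measuring a tendency. For the NGRO this is a fair reason not to class it as mood-dependent. For the others, retest stability does not show that scores are unaffected by a current episode.
- **Duration of the current episode is only said to be assessed.** No passage enters it into a regression. With the dates of birth and completion it could help place onset before or after the birth. This is right, and that use should be kept. The remaining issue is its place under Risk factors, with a justification in terms of development.
- **Choice and order of predictors belong to the analysis plan.** Generally true. The point here is what the article asserts can be concluded, which it states positively.

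A reader might also infer that a single model will hold all factors together, or that risk factors will be modelled in fathers alone. The article says neither. Analyses refers to regressions in the plural, and most scales go to both groups. No criticism is built on either reading.

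**Conclusion.** The point holds for the concurrently rated factors. For these the survey supports statements about correlates of current depressive symptoms, and the Discussion's claim about development goes beyond the design. Presenting simultaneous measurement of risk factors as a strength, with no mention of reverse causation, is a misstatement.

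Two stronger readings are tempting. One is that the study cannot identify any risk factor. The documents do not support this, because previous episodes, socio-demographic data and the circumstances of pregnancy and birth have a plausible time order. The other is that consequences of depression will be reported as causes. That is a prediction; the wording elsewhere in the article leaves room for a careful report.

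The size cannot be fixed from the documents. Under the stated assumptions (92 cases, 1058 non-cases, no causal role, two-sided 0.05), the chance of a misleading significant association runs from 15% at a shift of 0.1 SD to over 99% at 0.5 SD. The effect is confined to a secondary objective and the treatment-directed conclusion drawn from it. The primary comparison of prevalence is untouched.

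**What to change.** - Before modelling, divide the Table 1 factors into antecedent and concurrent. Assign the unclear rows (NGRO, involvement, maternal diagnosis) one by one with a reason.
- In the logistic regressions, fit and report the antecedent factors first, without the concurrent scales. Call only these potential risk factors, and note that they rest on recall.
- Report GSE, social support, ASA-27, ASI, sleep quality and the three health ratings separately, as correlates of current symptoms.
- Do not use duration of the current episode as a predictor of the outcome. Use it, with the dates of birth and completion, only to describe whether onset fell before or after the birth.
- In the Discussion, replace the claim about development with antecedent factors associated with, and correlates of, PPD. Limit the stated benefit of simultaneous measurement to comparability between groups. Add temporal order and reverse causation to the limitations.

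The cost is analysis order and wording, with no new data. Trial status reports analysis still under way in August 2019, so at that date the change was feasible. The price is a more modest secondary claim.

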## Data Availability

Not applicable.

## Abbreviations

ASA-27: Adult Separation Anxiety Questionnaire
ASI: Anxiety Sensitivity Index
c.f.: compare with
CSSRI-D: German version of the Client Sociodemographic and Service Receipt Inventory
DEGS: German Health Interview and Examination Survey for Adults
DNA: Deoxyribonucleic acid
e.g.: for example
et al.: and others
etc.: et cetera
FIMA: questionnaire for health-related resource use in the elderly population
F-SozU-K-14: Social Support Questionnaire
GSE: General Self-Efficacy scale
NGRO: Questionnaire of Normative Gender Role Attitudes
PHQ-9: Patient Health Questionnaire
PPD: Paternal postpartum depression
Tab.: Table
vs.: versus
WHO-5: World Health Organization – Five Well-Being Index
